##### Diet

Plasma carotenoids will be measured as an objective marker of fruit and vegetable intake. Self-reported dietary intake will be measured at each time point using a version of the previously validated EPIC Food Frequency Questionnaire^31^ that has been adapted for a 6-month recall period. This will be administered as part of the self-report questionnaires.

#### Self-report questionnaires

Participants will complete a demographics questionnaire at baseline based on Progress-Plus^32^ factors (place of residency, race/ethnicity, occupation, gender/sex, religion, education, socioeconomic status, social capital, age, disability, relationship status, caring responsibilities, car ownership, access to the internet).

Self-reported behavioural and psychosocial measures will be collected via validated self-report questionnaires that can be completed on paper or online, at the participant’s preference. A full list of questionnaires can be found in table 1.

**Table 1 T1:** Questionnaires administered in the GLoW trial

Domain	Measure	Time point
Demographics	Bespoke questionnaire based on PROGRESS-Plus^32^	Baseline
Health-related quality of life	EQ-5D-5L^24 25^	All
Capability/well-being	ICECAP-A^26 27^	All
Diabetes-related quality of life	Audit of Diabetes Dependent Quality of Life^35^	All
Health/social care use	Bespoke resource use questionnaire	All
Food cravings	Control of Eating Questionnaire^36^	All
Dietary restraint	Three Factor Eating Questionnaire—Restraint subscale^37^	All
Binge eating	The Binge Eating Scale^38 39^	All
Dietary intake	Food Frequency Questionnaire^31^	All
Physical activity	Recent Physical Activity Questionnaire^29 30^	All
Intervention adherence	Bespoke questionnaire	6 months

GLoW, Glucose Lowering through Weight management.

#### ​Intervention adherence

Adherence data for the tailored DEW (including attendance at weekly WW meetings and remote education sessions, and use of online tools) will be collected by WW as part of an established system for NHS contracts. Self-reported intervention adherence for both programmes will also be collected via a self-report questionnaire.

#### ​Medical notes review

Healthcare resource use will be obtained for all participants via medical notes review and registry data. Primary care records will be used to extract numbers of visits to the GP and community healthcare workers (defined as any primary or community-based health worker such as nurse and allied health professional contacts noted in the patient’s record) and prescribed medications. Last recorded weight, HbA_1c_ value, smoking status and diabetes status will also be extracted. This will help to minimise missing data from missed assessment appointments.

The notes review will be carried out at each study visit and following the end of the study by a research nurse blind to intervention allocation.

Baseline visit: notes review to cover the 3 months prior to study start6-month visit: notes review to cover from baseline up to 6 months.12-month visit: notes review to cover from 6 months to 12 months

We will obtain consent to conduct future notes reviews after the study has completed (up to 15 years poststudy) for future studies of long-term outcomes.

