#### ​Anthropometric measures

Anthropometric measurements will be made at participating primary care practices or research centres by research-trained healthcare professionals (hereafter ‘research nurses’) blind to intervention allocation, in line with standardised operating procedures. Participants will be asked to remove shoes and heavy clothing items. Height will be measured in centimetres using a mounted stadiometer (make and model dependent on practice). Where possible, weight (kg) and body fat percentage will be measured using a calibrated Tanita segmental body composition analyser (Tanita Ltd; MA Tokyo, Japan; model dependent on practice) which will be provided to practices by the research team. Where we have an insufficient number of Tanita scales to measure body fat at a practice, we will measure weight (kg) only using calibrated electronic scales (model dependent on practice). To maximise the number of participants for whom we can measure body fat, we will prioritise the use of Tanitas at large practices with a large number of eligible patients, and Clinical
Research Networks (CRN)-led practices (as CRN nurses can transport the Tanita scales to numerous practices). Blood pressure will be measured three times in a resting state using a calibrated OMRON automatic blood pressure monitor (OMRON Healthcare UK, Milton Keynes, UK; model dependent on practice).

If a research nurse is not available to conduct follow-up assessments, assessments may be conducted by trained research centre staff. If participants are unable to attend follow-up appointments at a participating practice, the research team may offer appointments at the local hospital or research centre, or home visits. Participants who are unable or unwilling to attend a visit will be asked to provide a self-measured weight. All other participants will also be asked for a self-measured weight at the time of appointment booking to enable us to quantify the degree of misreporting of self-measured weights.

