#### ​Method of implementing the allocation sequence

When participant eligibility has been confirmed at the baseline visit, the practice will inform the study coordinator. The study coordinator will enter the participant’s details into the trial database which will automatically assign an intervention to the participant.

The study coordinator (or member of their team) will write to the participant to inform them of their intervention allocation and will also inform the participant’s GP. The study coordinator or the GP (depending on practice and intervention allocation) will also send a referral form to the intervention provider, giving the details of the participant who has been referred to them.

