#### ​Blinding

Given the nature of the intervention, it is not possible to blind participants to their intervention group. GPs will be informed of the intervention allocation and participants will be allowed to discuss the intervention with their GP, as they would outside a trial scenario. However, participants will be asked not to reveal their intervention group to outcome assessors (ie, research nurses taking measurements). The trial statistician and the investigators will be blinded to intervention allocation until the database is locked and the primary analysis is complete.

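### The follow-up notes review is described as blind, but the reviewer reads the record of a GP who knows the arm, so assessor blinding cannot be assured from the 6-month review onward

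*Protocol article*

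**What the plan says.** All references are to the protocol article.

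- **Medical notes review.** The notes are reviewed at every visit and again "following the end of the study by a research nurse blind to intervention allocation". The source is the GP record: "Primary care records will be used to extract numbers of visits to the GP and community healthcare workers", together with prescribed medications. Last recorded weight, HbA1c, smoking status and diabetes status are also taken, with the stated purpose "This will help to minimise missing data from missed assessment appointments". The 6-month review spans baseline to 6 months; the 12-month review spans months 6 to 12.
- **Method of implementing the allocation sequence.** The study coordinator or a member of the coordinator's team "will write to the participant to inform them of their intervention allocation and will also inform" the GP. Either the coordinator or the GP then sends the referral form, and which of them does so varies with the practice and with the arm.
- **Blinding.** "GPs will be informed of the intervention allocation and participants will be allowed to discuss the intervention with their GP". Participants are asked not to tell outcome assessors which group they are in. The Trial Steering Committee section repeats that GPs are not blind.
- **Anthropometric measures.** Weight, body fat and blood pressure are measured by staff labelled research nurses, also said to be blind. If no nurse is available at follow-up, "assessments may be conducted by trained research centre staff".

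**The concern.** The article makes a positive statement that the notes reviewer is blind, while its own procedures send that reviewer into a record kept by someone who knows the arm. An allocation notice, a referral to one of the two programmes or a consultation note about the programme could each disclose the group.

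The label used for the reviewer is also the label for the people who measure three of the secondary outcomes. Disclosure at the 6-month review could therefore carry over to measurements, in particular those at 12 months. At stake is whether readers may treat weight, body fat, blood pressure and the items abstracted from the notes as blinded outcomes, as the single-blind description invites them to do.

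**Working it through.** No figure in the article bears on this point, so the check sets the passages side by side.

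**1. When could the record start to show the arm?** Allocation follows confirmation of eligibility at the baseline visit, and the baseline notes review looks back over the 3 months before study start. That review is not exposed. The letter to the GP, any referral and any discussion with the GP come after allocation. The first two would be expected early in the baseline-to-6-month window, which is the window the 6-month review reads.

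**2. Would the review task bring the reviewer into contact with it?**
- The reviewer counts contacts with GPs, nurses and allied health professionals noted in the record. The control programme is delivered by two trained healthcare professionals in healthcare or community venues (Diabetes education); the other programme is delivered by WW. A recorded attendance at the control programme could disclose the arm through the counting itself.
- Because the sender of the referral depends partly on the arm, even the presence or absence of a GP referral may be informative.
- Patient identification describes record alerts triggered by attempted referral to diabetes education, so referral activity does interact with the patient record.

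**3. Does any stated safeguard cover this route?** The request to participants covers what they say to assessors. The article states nothing about masking the notes, separating reviewer from measurer, or the order of the two tasks. At 12 months, order within the visit would not be enough: a nurse who did that participant's 6-month review has already read the allocation period.

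**4. Which outcomes are exposed?**

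| Outcome | How obtained | Exposure by this route |
|---|---|---|
| HbA1c (primary) | Central laboratory, barcoded tube | Little; the article does not specify how a value taken from the notes would be used |
| Weight, body fat | Calibrated scales, read by staff | Some; limited discretion |
| Blood pressure | Automatic monitor, three readings | Some; limited discretion |
| Remission | HbA1c plus at least 2 months without glucose-lowering medication | Some, if medication status comes from the notes; the outcome definition does not name its source |
| Resource use, diabetes status | Abstracted from the notes | Direct, since the abstractor may know the arm |

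**5. What is not stated.** The article does not say that the allocation is filed in the part of the record being read, that one nurse both reviews and measures the same participant, or that the review precedes the measurements.

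**The case against.** The strongest reply is that harm needs a chain of events, none of which the article states. The arm must be visible in the notes. The reviewer must also be that participant's measurer. The review must come first, or be remembered six months later. A diabetes-education referral need not be revealing either: practices already refer to that programme as standard care, and patients are found through its waiting lists, so such entries can predate randomisation in both arms. The devices leave little discretion, prescriptions are largely factual, and the trial statistician and investigators are separately stated to be blinded until the primary analysis is complete. Finally, a condensed article may leave task order to operating procedures.

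Most of this stands, and it limits the conclusion. A reader might infer that assessor blinding is lost for every participant and that the single-blind design is not delivered. The article does not support that, because each link in the chain is an inference. A reader might also infer that stand-in assessors are the people who send allocation letters. The article says only that they are trained research centre staff and shows no overlap with the coordinator's team.

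The appeal to omitted detail does not dispose of the point. The article affirms blindness for a task that, on its stated schedule, reads a record likely to reveal the arm, and the safeguard it does state addresses another route.

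**Conclusion.** The point holds as an unprotected risk, not as a demonstrated loss of blinding. From the 6-month notes review onward, the blinding of the notes reviewer cannot be assured. Nor can that of the staff group measuring weight, body fat and blood pressure.

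The primary outcome is largely protected by central assay. The article gives no basis for sizing any bias in the secondary outcomes, and automatic devices probably limit it. How many participants are affected is also unknown.

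The conclusion rests on two assumptions: that allocation or referral information reaches the record the reviewer opens, which is likely but not stated, and, for the measured outcomes, that the reviewer and measurer are sometimes the same person. Since the remedy is cheap, the change should be made, but the primary analysis does not depend on it.

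**What to change.** 1. At each visit, complete and record all measurements before any record is opened.
2. Do the 0–6 and 6–12 month notes reviews, using dated entries, after that participant's 12-month measurements are recorded. Alternatively, if existing staffing allows, have the reviews done by someone who does not measure that participant.
3. Have assessors record at each follow-up visit whether they know the arm, and report the result by group.
4. Do not describe the follow-up notes review as blinded unless steps 1 and 2 secure it.
5. As a precaution, staff who handle allocation letters should not act as stand-in assessors.

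**Cost.** Existing tasks are re-ordered and one item is added to the visit form. The 6-month resource-use data arrive about 6 months later, and the 6-month values for last recorded weight and HbA1c must be retrieved by date. The article describes no interim use of these data: the economic evaluation is a 12-month analysis and there are no early-stopping rules.

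Recruitment began in July 2018, so some 6-month reviews may have fallen due from January 2019. For participants already reviewed, what remains is to use a different measurer at 12 months where possible and to record the assessor's knowledge of the arm.

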#### ​Administrative and registry data

We will obtain consent at baseline for future collection of administrative and registry data on health event and healthcare usage information (up to 15 years poststudy). Outcomes will include hospital episode statistics, cardiovascular events, stroke, myocardial infarction, cancer and death and will be obtained from NHS digital, the Healthcare Quality Improvement Partnership and the National Cancer Registration and Analysis Service. This will allow us to evaluate the longer term impact of these programmes on diabetes-related and weight-related morbidity and mortality.

#### ​Qualitative interviews

Around the time of the 6-month follow-up, we will conduct semi-structured interviews with participants from both intervention arms (n≥26). Participants will be recruited in a 2:1 ratio (DEW:DE), as we are interested in comparing the experience of the two groups, but we expect the group receiving the DEW programme to provide the richest data on the experiences of weight loss and weight loss maintenance. Participants will be purposively sampled (demographic characteristics, programme attendance/adherence, weight change). We will also conduct interviews with treatment providers (n≥12) to understand their experience of delivering the intervention. Interviews will be conducted by a trained research associate and audio recorded.

Questions will focus on exploring:

How did participants and practitioners experience the programme and its components: (1) education; (2) WW meetings; (3) digital tools and (4) remote dietetic counselling?What were the causal mechanisms and contextual factors that were associated with different outcomes?What were the needs of participants at the end of the programme?What were the facilitators and barriers to maintaining behavioural change?

### Recruitment and enrolment

#### ​Recruitment of practices

Primary care practices will be identified and recruited by the CRN. Participating practices must be currently referring patients with a recent diagnosis of T2D to structured DE (DESMOND) as part of standard practice and should have active WW meetings in the local area. They should also be research active with the capacity to recruit and follow-up participants. The CRN will attempt to recruit practices from diverse areas using known characteristics of the practice population to enable recruitment of a sample broadly representative of the target population (UK adults with overweight and obesity and who have a recent diagnosis of T2D).

#### ​Patient identification

Eligible patients will be identified through electronic searches of primary care records and waiting lists for DE. GPs will write to all potentially eligible patients inviting them to participate. This letter will include a participant information sheet and details of how to contact the study team at the research centre. Participants will also receive opportunistic invitations during routine consultations via an invitation letter and participant information sheet to take home with them. Pop-up alerts on patient records (triggered by diagnosis or attempted referral to DE) will be implemented to facilitate opportunistic recruitment. To boost enrolment, advertisements will also be placed in local pharmacies, news media and other relevant settings.

#### ​Enrolment

Patients willing to participate will be asked to contact the research centre for more information. This can be by telephone, email or reply slip. Research centre staff will answer any questions and conduct a telephone screening. If patients are eligible and willing to participate, the research staff will check that they have received the participant information sheet (sending another if they have not) and arrange a baseline assessment with the research nurse at a local participating practice or research centre.

At the baseline visit, the research nurse will take informed consent. This will include ensuring that participants have read the information sheet and had the opportunity to ask questions. They will also confirm eligibility, including an objective measure of height and weight, before taking the rest of the baseline measurements. At the end of each day, the research nurse will email the study coordinator a list of participants who have formally enrolled on the trial.

### Randomisation

#### ​Randomisation sequence

Participants will be allocated to one of the two intervention arms in a 1:1 allocation using individual-level blocked randomisation stratified by sex (men, women) and duration of diabetes (<1 year, 1–3 years) with a block size of 6. The randomisation sequence will be computer-generated by the trial statistician and the randomisation process implemented by the data manager. The sequence will be unknown to all other personnel, including study coordinators, outcome assessors and investigators.

#### ​Method of implementing the allocation sequence

When participant eligibility has been confirmed at the baseline visit, the practice will inform the study coordinator. The study coordinator will enter the participant’s details into the trial database which will automatically assign an intervention to the participant.

The study coordinator (or member of their team) will write to the participant to inform them of their intervention allocation and will also inform the participant’s GP. The study coordinator or the GP (depending on practice and intervention allocation) will also send a referral form to the intervention provider, giving the details of the participant who has been referred to them.

#### ​Blinding

Given the nature of the intervention, it is not possible to blind participants to their intervention group. GPs will be informed of the intervention allocation and participants will be allowed to discuss the intervention with their GP, as they would outside a trial scenario. However, participants will be asked not to reveal their intervention group to outcome assessors (ie, research nurses taking measurements). The trial statistician and the investigators will be blinded to intervention allocation until the database is locked and the primary analysis is complete.

### Statistics and data analysis

#### ​Sample size calculation

The primary outcome is 12-month change from baseline in HbA_1c_. Based on data from a previous trial in adults with a recent diagnosis of T2D,^33^ we assumed a 16 mmol/mol SD, a 0.8 correlation between baseline and follow-up and 25% attrition. In a US trial of a similar intervention in people with T2D of any duration, a difference of 4 mmol/mol was observed between intervention (−3 mmol/mol) and control (+1 mmol/mol) at 12 months.^23^ We need 576 participants to detect a difference between randomised groups of 3 mmol/mol HbA1c with 90% power at a 5% significance level.

#### ​Statistical analysis plan

A detailed statistical analysis plan will be developed and signed off by the Trial Steering Committee (TSC) prior to analysis. Participants will be analysed in the group to which they were randomised, based on the intention-to-treat principle. The intervention effect, representing the baseline-adjusted difference in change from baseline to 12 months in HbA_1c_ between the intervention and control group, will be estimated using a linear regression model including randomisation group, baseline value of HbA_1c_ (ie, analysis of covariance (ANCOVA)) and the randomisation stratifiers (sex, duration of diabetes). The missing indicator method^34^ will be used to ensure inclusion of participants with a missing baseline value of HbA_1c_. Participants with missing values of HbA_1c_ at 12 months will be excluded (ie, a complete-case analysis). If there are >5% of participants with missing values of HbA_1c_ at 12 months, a sensitivity analysis will be performed using multiple imputation by chained equations; full details of this analysis will be provided in the statistical analysis plan.

Continuous secondary outcomes will be analysed using the method described earlier. Binary secondary outcomes will be analysed using a logistic regression model including randomisation group and the randomisation stratifiers.

For the primary outcome, effect modification by (1) sex, (2) index of multiple deprivation (high, low), (3) educational qualification (below postsecondary, postsecondary and above postsecondary) and (4) duration of diabetes (<1 year; 1–3 years) will be tested using an F-test of the relevant multiplicative interaction parameter in the ANCOVA model. If the p value for a particular interaction is <0.05, then the intervention effect and 95% CI will be estimated within the relevant subgroups.

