#### Inclusion criteria

Body mass index≥25 kg/m^2^.Age≥18 years.Diagnosis of T2D within the previous 36 months (confirmatory blood test will not be required).Capable of giving informed consent.Have a good understanding of the English language (study materials are not tailored to support non-English language speakers).Willing to be randomised.Willing to attend follow-up visits at a local participating general practitioner (GP) practice or research centre.

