#### ​Secondary outcomes

The 6-month change from baseline in HbA_1c_.

The 6-month and 12-month changes from baseline in body weight, body fat percentage, systolic and diastolic blood pressure, total cholesterol, high-density lipoprotein cholesterol and low-density lipoprotein cholesterol.

Good glycaemic control (HbA_1c_ <53 mmol/mol) at 6 and 12 months.

Remission from diabetes (HbA_1c_ <48 mmol/mol and without glucose-lowering medication for ≥2 months) at 6 and 12 months.

Weight loss ≥5% and ≥10% of initial body weight at 6 and 12 months.

Modelled cardiovascular risk (UKPDS) at 12 months.

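### The logistic models for good glycaemic control and remission leave out baseline HbA1c: a valid test, but less precise than the collected data allow

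*Protocol article*

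**What the plan says.** The Secondary outcomes section defines two binary outcomes from HbA1c: "Good glycaemic control (HbA_1c_ <53 mmol/mol) at 6 and 12 months" and "Remission from diabetes (HbA_1c_ <48 mmol/mol and without glucose-lowering medication for ≥2 months) at 6 and 12 months". Both describe status at the visit.

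The Statistical analysis plan section states their model in full: "Binary secondary outcomes will be analysed using a logistic regression model including randomisation group and the randomisation stratifiers". The same section names the stratifiers as sex and duration of diabetes.

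The other outcomes are treated differently. The primary effect "will be estimated using a linear regression model including randomisation group, baseline value of HbA_1c_ (ie, analysis of covariance (ANCOVA"), and "Continuous secondary outcomes will be analysed using the method described earlier", so all continuous outcomes are adjusted for baseline.

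On entry, the Inclusion criteria ask for "Diagnosis of T2D within the previous 36 months (confirmatory blood test will not be required") and set no HbA1c minimum. Among users of glucose-lowering drugs, the Exclusion criteria rule out only those on insulin.

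**The concern.** Good glycaemic control, and the HbA1c part of remission, are cut-points of the primary outcome variable. The sample size treats baseline HbA1c as explaining 0.8² = 64% of the variance at follow-up, yet the models for the cut-points omit it. Because entry has no HbA1c floor, some participants can be below 53, or below 48 and off medication, on the day they enrol. They can then count as successes at 12 months without any change.

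Two things are at stake. The comparisons of control and remission are less precise than they could be. They also move with any chance difference in baseline HbA1c between the arms, while the primary analysis corrects for it. The threshold results and the primary result could then appear to disagree for no reason other than baseline imbalance.

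**Working it through.** **Inputs from the protocol** (Sample size calculation, Trial design): SD 16 mmol/mol, correlation 0.8, attrition 25%, difference 3 mmol/mol, power 90%, significance level 5% (taken as two-sided), 1:1 allocation, 576 participants.

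**Inputs assumed:** normally distributed HbA1c; baseline mean of 48, 53, 58 or 63 mmol/mol (the documents give none); no mean change in the control arm.

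**Step 1: reproduce 576.** Residual SD after baseline adjustment = 16 × √(1 − 0.8²) = 9.6. Per arm, n = 2 × (1.960 + 1.282)² × 9.6² / 3² = 215.2, so 216; the total is 432, and 432 / 0.75 = 576. This matches exactly. Without baseline adjustment (SD 16) the same formula gives 598 per arm, 1,196 in total and 1,196 / 0.75 = 1,595. The trial's size therefore depends on using baseline HbA1c.

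**Step 2: share already below threshold at entry.** This is Φ((threshold − mean) / 16). For <53 it runs from Φ(5/16) = 62% at mean 48 to Φ(−10/16) = 27% at mean 63. For <48 it runs from Φ(0) = 50% to Φ(−15/16) = 17%.

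**Step 3: power for the cut-points.** Simulation with 216 per arm and 2,000 trials per row: 12-month HbA1c = mean + 0.8 × (baseline − mean) + N(0, 9.6) − 3 × arm, cut at the threshold. Logistic regression on group and two binary stratifiers was fitted with and without continuous baseline HbA1c.

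| Threshold | Baseline mean | Below at 12 months, control / intervention | Of those below at 12 months, already below at baseline | Power as planned | Power with baseline HbA1c |
|---|---|---|---|---|---|
| <53 | 48 | 62.2% / 69.2% | 82% | 32.3% | 51.5% |
| <53 | 53 | 50.0% / 57.3% | 77% | 32.7% | 53.3% |
| <53 | 58 | 37.8% / 45.0% | 71% | 34.3% | 52.3% |
| <53 | 63 | 26.6% / 33.1% | 65% | 32.1% | 48.7% |
| <48 | 48 | 50.0% / 57.3% | 77% | 32.6% | 53.3% |
| <48 | 53 | 37.7% / 45.0% | 71% | 32.7% | 52.3% |
| <48 | 58 | 26.6% / 32.9% | 65% | 30.6% | 46.9% |
| <48 | 63 | 17.4% / 22.6% | 59% | 26.8% | 41.4% |

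Hand check of the second row: the pooled proportion is 0.5365, SE = √(2 × 0.5365 × 0.4635 / 216) = 0.048, z = 0.073 / 0.048 = 1.52, and power = Φ(1.52 − 1.96) = 33%.

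Separate runs, with baseline means inside the same range, widen these figures slightly: 32-36% against 49-54% for <53, and 27-34% against 41-55% for <48.

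**Step 4: sensitivity to the correlation.** At 0.5 in place of 0.8, the gain is about 4-6 points (for example 34.8% to 38.7% for <53 at mean 53).

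**Step 5: validity.** With no effect, at mean 53 and threshold 53, the false-positive rate over 4,000 trials is 5.2% without baseline and 5.1% with it. In the roughly 31% of null trials where the arms differ at baseline by more than one standard error (16 × √(2/216) = 1.5 mmol/mol), it is about 10-12% without baseline and about 5% with it. Trials with closer balance offset this, so the overall rate stays at 5%.

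**The case against.** The strongest reply is that nothing here is invalid. Randomisation makes the planned comparison of status at the visit sound, the overall error rate is nominal, and chance imbalance is ordinary sampling variation that the standard error already covers. HbA1c is also analysed as a continuous, baseline-adjusted outcome at 6 and 12 months, so the efficient inference on the same measurements is already planned. The trial is not powered on any binary outcome. All of this stands, and it limits the point to precision in secondary analyses.

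Other limits also stand. The share already below threshold depends on a baseline mean and a distribution that the documents do not give. The medication part of remission was not simulated, so no power figure applies to the full definition. Baseline HbA1c may be missing for some participants, since the protocol provides a missing-indicator method for that case.

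Two stronger readings are tempting and are not supported:

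- **The wrong quantity is estimated.** A reader might infer this because the objectives speak of achieving control or remission. The outcome definitions are status at 6 and 12 months, and the planned model compares exactly that. Adding baseline HbA1c would not turn status into new achievement.
- **The weight-loss outcomes share the problem.** They are defined as "Weight loss ≥5% and ≥10% of initial body weight at 6 and 12 months", so nobody meets them at entry. A simulation with assumed mean losses of 2 and 4 percentage points and SD 6 gave power of 76-78% without baseline weight and 76-79% with it.

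Deferral to the later statistical analysis plan does not remove the point, because the protocol already states which terms the model contains.

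**Conclusion.** The point holds as an inexpensive gain in precision for two secondary outcomes. The planned logistic models are valid but inefficient. On the protocol's own SD, correlation, effect and number of completers, adding baseline HbA1c raises power by about 15-21 points in the tabulated settings, both for HbA1c <53 and for the HbA1c <48 component of remission. That rests on normal data, an assumed baseline mean of about 48 to 63 mmol/mol and the 0.8 correlation; at 0.5 most of the gain disappears. Power for remission as defined depends on medication rates that are not stated. The primary analysis, the continuous outcomes and the weight-loss outcomes are unaffected.

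**What to change.** - Add continuous baseline HbA1c to the logistic models for HbA1c <53 and for remission, at 6 and 12 months, handling missing baseline values with the same missing-indicator method as the primary model.
- For remission, also add baseline use of glucose-lowering medication (yes/no). Prescribed medications are already extracted in the baseline notes review, which covers the preceding 3 months.
- Adjustment changes the odds ratio from a marginal to a conditional one, so also report the standardised risk difference with its 95% CI. This suits objectives worded as probabilities.
- Tabulate, by arm, how many participants met each criterion at baseline. This lets readers separate new from pre-existing control or remission, which adjustment alone does not do.

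Leave the weight-loss models as they are. The cost is a short addition to the analysis plan before sign-off, a standardisation step in the analysis and one extra table. No new data are needed.
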